# Accuracy and Cost-effectiveness of Technology-Assisted Dietary Assessment Comparing the Automated Self-administered Dietary Assessment Tool, Intake24, and an Image-Assisted Mobile Food Record 24-Hour Recall Relative to Observed Intake: Protocol for a Randomized Crossover Feeding Study

**DOI:** 10.2196/32891

**Published:** 2021-12-16

**Keywords:** 24-hour recall, Automated Self-Administered Dietary Assessment Tool, Intake24, mobile food record, image-assisted dietary assessment, validation, controlled feeding, accuracy, dietary measurement error, self-report, energy intake, adult, cost-effectiveness, acceptability, mobile technology, diet surveys, mobile phone

## Abstract

**Background:**

The assessment of dietary intake underpins population nutrition surveillance and nutritional epidemiology and is essential to inform effective public health policies and programs. Technological advances in dietary assessment that use images and automated methods have the potential to improve accuracy, respondent burden, and cost; however, they need to be evaluated to inform large-scale use.

**Objective:**

The aim of this study is to compare the accuracy, acceptability, and cost-effectiveness of 3 technology-assisted 24-hour dietary recall (24HR) methods relative to observed intake across 3 meals.

**Methods:**

Using a controlled feeding study design, 24HR data collected using 3 methods will be obtained for comparison with observed intake. A total of 150 healthy adults, aged 18 to 70 years, will be recruited and will complete web-based demographic and psychosocial questionnaires and cognitive tests. Participants will attend a university study center on 3 separate days to consume breakfast, lunch, and dinner, with unobtrusive documentation of the foods and beverages consumed and their amounts. Following each feeding day, participants will complete a 24HR process using 1 of 3 methods: the Automated Self-Administered Dietary Assessment Tool, Intake24, or the Image-Assisted mobile Food Record 24-Hour Recall. The sequence of the 3 methods will be randomized, with each participant exposed to each method approximately 1 week apart. Acceptability and the preferred 24HR method will be assessed using a questionnaire. Estimates of energy, nutrient, and food group intake and portion sizes from each 24HR method will be compared with the observed intake for each day. Linear mixed models will be used, with 24HR method and method order as fixed effects, to assess differences in the 24HR methods. Reporting bias will be assessed by examining the ratios of reported 24HR intake to observed intake. Food and beverage omission and intrusion rates will be calculated, and differences by 24HR method will be assessed using chi-square tests. Psychosocial, demographic, and cognitive factors associated with energy misestimation will be evaluated using chi-square tests and multivariable logistic regression. The financial costs, time costs, and cost-effectiveness of each 24HR method will be assessed and compared using repeated measures analysis of variance tests.

**Results:**

Participant recruitment commenced in March 2021 and is planned to be completed by the end of 2021.

**Conclusions:**

This protocol outlines the methodology of a study that will evaluate the accuracy, acceptability, and cost-effectiveness of 3 technology-enabled dietary assessment methods. This will inform the selection of dietary assessment methods in future studies on nutrition surveillance and epidemiology.

**Trial Registration:**

Australian New Zealand Clinical Trials Registry ACTRN12621000209897; https://tinyurl.com/2p9fpf2s

**International Registered Report Identifier (IRRID):**

DERR1-10.2196/32891

## Introduction

### Background

Dietary intake surveillance enables monitoring of diet-related health and nutritional status of populations and provides vital data to inform public health nutrition policies and programs [1]. Therefore, accurate assessment of dietary intake is important to assist effective government decision-making on dietary advice and programs by defining the extent of the problem and possible solutions. The 24-hour dietary recall (24HR) is the current standard and preferred method for large-scale population surveillance to assess absolute dietary intakes [2-6]. Technology-assisted 24HR offers the potential to improve accuracy and reduce participant and researcher burden. However, the relative accuracy, acceptability, and cost of various technology-assisted methods are unclear. Population dietary surveillance studies typically include thousands of participants. As such, cost and personnel requirements are major determinants of the feasibility of a dietary assessment method. However, information on the cost of method administration has rarely been collected or published. This information would contribute to the feasibility assessment by researchers and decision makers.

A 24HR method is designed to capture detailed information on foods and beverages consumed on the previous day or during the previous 24 hours and is traditionally conducted as a structured face-to-face interview [7]. The 24HR method is a complex process involving numeracy, perception, memory, and the conceptualization of that memory [8]. The benefits of 24HR methods over less burdensome methods, such as food frequency questionnaires, include the detailed accounting of all foods and beverages consumed and information on context (eg, meal timing). This information allows the examination of questions related to different dietary components, dietary patterns, and meal patterning [9].

Various methods have been developed to enhance recall and reduce errors in reported intake. For example, the National Health and Nutrition Examination Survey in the United States includes an interviewer-administered Automated Multiple-Pass Method (AMPM) 24HR [3] as does the Australian Health Survey [2]. AMPM is a web-based interface designed for surveillance, typically implemented in-person by a trained interviewer, which adds to the cost of undertaking large-scale surveys. The AMPM provides a structured interview format with specific probes in 5 structured sets *or passes*: a quick list, forgotten foods pass, time and occasion pass, detail pass, and final review [10]. Portion size estimation is addressed using a food model booklet. More recently, web-based interfaces have been developed to enable self-administration of the 24HR method by participants, removing the need for trained interviewers and reducing study costs.

Automated web-based, self-administered 24HR methods begin with a quick list. Details are collected using a sequence of probes, and standard images of foods or models are used to help participants estimate portion sizes. The format and number of images are informed by user testing [11,12]. These methods include the US-developed Automated Self-Administered Dietary Assessment Tool (ASA24) and the UK-developed Intake24. ASA24 is an adaptation of AMPM and was developed by the United States National Cancer Institute based on input from stakeholders in an external working group, along with cognitive and usability testing [13]. Intake24 was developed by Newcastle University, United Kingdom, using 4 cycles of user testing, with modification after each cycle, in adolescents and young adults [12,14]. Similar levels of measurement error have been observed in web-based self-administered 24HR methods (Intake24 and ASA24) and in interviewer-administered methods as determined by objective measures of energy intake using doubly labeled water [15,16]. This suggests that the additional costs associated with interviewer-administered methods in the form of trained interviewers and coders may not translate to improved accuracy. However, to date, no study has evaluated the differences in accuracy between Intake24 and ASA24.

Using image-assisted methods to supplement the 24HR method has the potential to reduce recall bias, with images used to assist food identification and portion size estimation. In recent reviews, image-assisted approaches, including 24HR methods, resulted in greater accuracy of self-reported dietary intake when compared with the accuracy of methods without images supplied by participants [17-19]. The Image-Assisted mobile Food Record 24-Hour Recall (mFR24) is a mobile app developed by Purdue University. Participants are instructed to take *before* and *after* images of all food and beverages consumed and to include a fiducial marker (an object of known shape, size, and color) [20] in each image to aid in portion size verification. The content of the images is confirmed either by a human trained analyst or by automated methods using computer vision and machine learning (eg, deep learning) techniques [21-23]. In contrast to other image-assisted 24HR methods in which the image review occurs toward or at the end of the interview [24-28], the image review in mFR24 begins at the start of the interview based on participant feedback from pilot testing. This novel approach has yet to be evaluated for its accuracy and acceptability. Furthermore, the accuracy and acceptability of the mFR24 has not been compared with either the web-based self-administered ASA24 or Intake24 in the same study population.

To continue to improve upon dietary assessment, there is an urgent need for studies that enable the understanding and mitigation of measurement errors [29]. The error in dietary intake estimation can be identified by comparing reported intake with recovery biomarkers, such as doubly labeled water as a measure of true energy intake [30]. However, such methods are limited to energy or single nutrients and do not identify specific foods and beverages that are omitted or inaccurately reported. Controlled feeding studies allow for the examination of measurement errors at the level of foods and beverages. Studies with measures of known food and beverage intake enable the understanding of factors contributing to misreporting, such as omission of particular types of foods, intrusions, inaccurate portion size estimation, and incorrect food descriptions [31-35]. For example, Kirkpatrick et al [33] found that more intrusions (items not consumed) were present with the use of a web-based self-administered 24HR method than in an interviewer-administered 24HR method. Widaman et al [35] found no statistically significant differences between estimated and observed intake of grain foods using web-based self-administered 24HR methods, although all other food groups were overestimated. These findings illustrate how controlled feeding studies can provide insights into the mechanisms of dietary intake measurement errors that would otherwise remain unknown.

Various psychosocial factors have been associated with misreporting, including social desirability traits, restraint, disinhibition, fear of negative evaluation, and body weight and body image perceptions [36-38]. In a study conducted in the United States, measuring an array of psychosocial and demographic factors, Tooze et al [37] found that although these factors cumulatively accounted for 20% of the variability in misreporting in interviewer-administered 24HR methods, 80% remained unaccounted for. Clearly, other constructs associated with misreporting, psychosocial or otherwise, need to be identified, and it has been recommended that future research focuses on this [37,39]. For example, it is frequently stated that visual perception and conceptualization of memory are involved in reporting of intake [8], but these factors are not typically assessed in studies evaluating participant reporting accuracy. Furthermore, a better understanding of how psychosocial and cognitive factors map to various sources of error (eg, omissions and intrusion) could potentially help to minimize measurement error. To the best of our knowledge, no controlled feeding studies have evaluated the associations of psychosocial or cognitive factors in food and beverage reporting accuracy.

Social factors may also contribute to misreporting. Individual work patterns and lifestyles have rapidly changed with the increased use of screen-based work and leisure activities [40,41]. In a survey of over 12,000 households in Australia, 75% people reported that they always, often, or sometimes felt rushed or pressed for time [42]. With these rapid shifts in day-to-day life, the demands for traditional dietary assessment methods may be misaligned with people’s daily lives and expectations and may be viewed as inconvenient. Technology-based self-report dietary assessment methods enable remote completion using laptops or mobile devices and have been indicated as more acceptable to participants than traditional face-to-face methods [43-45]. For example, research conducted in the United States demonstrated that 70% preferred the ASA24 over the AMPM [46]. The acceptability of dietary assessment methods has important implications, especially in large-scale population studies, as it can impact response rates and therefore the representativeness and generalizability of the study sample [47,48]. Image-assisted 24HR methods, such as the mFR24, are yet to be fully evaluated for consumer acceptability and comparison with other technology 24HR methods such as Intake24 and ASA24.

### Objectives

This research protocol will compare 3 leading technology-assisted dietary assessment methods. Using a controlled feeding study design with healthy adults aged 18 to 70 years, this study will (1) compare the accuracy, acceptability, and cost-effectiveness of 3 technology-assisted 24HR methods (ASA24, Intake24, and mFR24) relative to observed intake for 3 meals on 1 day; (2) test the accuracy of automated methods for determining food and beverage intake using food images and image analysis, computer vision, and machine learning techniques; and (3) assess associations between reporting errors and demographic, psychosocial, and cognitive factors.

## Methods

### Sample and Recruitment

The sample will be selected from adults aged 18-70 years residing in Perth, the capital city of Western Australia, Australia, and recruited via the electoral roll by selecting postcodes that provide representation across socioeconomic status. Other recruitment methods will include advertising on the Curtin University website and a snowball methodology (eg, email newsletter and referrals from friends or colleagues). A final sample of 150 randomized participants (allowing for a 20% dropout) will allow for 90% power at a 5% significance level when the true difference between any 2 mean differences between estimated and observed dietary energy intake is 0. Quota sampling will be used to ensure that equal numbers of men and women are recruited. To be included in the study, participants must be able to attend in-person feeding sessions on 3 separate days and have access to a computer and a smartphone (running iPhone operating system or Android operating system) with a data plan. Exclusion criteria include serious illnesses or medical conditions, pregnancy, special dietary requirements, or dietary restrictions because of food allergies or intolerances or dieting to lose weight.

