### Study Design

A controlled feeding study with a crossover design will compare the accuracy of 3 technology-assisted methods of assessing 1 day of dietary intake: ASA24, Intake24, and mFR24. The sequence of the 3 dietary assessment periods will be randomized for each participant, with a 1-week washout period between each feeding session (Figure 1). Therefore, each participant will be exposed to each of the 3 methods at different periods. The crossover design, a repeated measurement design, will allow both between-group and within-group method comparisons. This design yields a more efficient comparison of treatments than a parallel design because fewer participants are required in the crossover design to attain the same level of statistical power or precision as a parallel design.

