### Data Analyses

#### Energy Intake Estimation Accuracy

The participant feeding days with at least two meals eaten at the food laboratory will be included in the analyses. Daily energy intake from each 24HR method and the controlled feeding sessions will be calculated, excluding any items reportedly consumed outside of the food laboratory. Outlier checks will be conducted to identify any obvious keying errors or food composition data anomalies, which will be corrected before proceeding. Bland-Altman plots will be used to test for agreement between the 24HR values and controlled feeding measures at the individual and group levels. Repeated measurements will be analyzed using the linear mixed models procedure using SPSS version 25, accounting for age, gender, and BMI, with 24HR method and method order as fixed effects, to assess whether there are statistically significant differences by 24HR method. Misreporting will be assessed by examining the ratio of reported 24HR intake to observed intake, with the lowest tertile considered to indicate underreporting. The proportion of underreporters in each 24HR method will be compared using chi-square tests and logistic regression. Among underreporters, the total energy misestimation will also be compared using regression models adjusted for age, gender, and BMI.

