#### Correlates of Energy Misestimation

Psychosocial, demographic, and cognitive factors associated with omission and intrusion rates and with energy misestimation on each 24HR method will be evaluated using chi-square tests and multivariate logistic regression. The effects of factors will be reported as odds ratios and associated 95% CIs. Some dietary factors in the Accuracy and Cost-effectiveness of Technology-Assisted Dietary Assessment study are standardized because of the controlled feeding methodology (meal frequency and eating location), but it is hypothesized that food and meal complexity and physical form will affect reporting accuracy via an interaction with cognitive factors. P<.05 will be considered statistically significant in all analyses.

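### The only power statement claims 90% power at a true difference of zero, where the planned test for differences between methods rejects only 5% of the time

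*Protocol article*

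**What the plan says.** The sample-size rationale is one sentence in the Protocol article, Methods, Sample and Recruitment. It takes 150 randomized participants, allows for 20% dropout, and claims "90% power at a 5% significance level when the true difference between any 2 mean differences between estimated and observed dietary energy intake is 0". The article has no other power statement.

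The analysis is in Data Analyses, Energy Intake Estimation Accuracy. Linear mixed models with 24HR method and method order as fixed effects, accounting for age, gender and BMI, are fitted "to assess whether there are statistically significant differences by 24HR method". The Methods part of the Abstract gives the models the same purpose. Correlates of Energy Misestimation sets the threshold: "P<.05 will be considered statistically significant in all analyses".

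Under Study Design, "each participant will be exposed to each of the 3 methods at different periods", so each completer contributes to every pairwise comparison of methods.

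**The concern.** Power is the probability of rejecting the null hypothesis at a stated alternative. For a test of difference, zero is the null itself, so the rejection probability there is the significance level and does not depend on sample size. A figure of 90% at zero can belong only to an equivalence test, which rejects when the difference is shown to lie inside a margin. The sample-size sentence therefore describes one question (are the methods equivalent?) and the analysis section tests another (do they differ?).

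Comparing the accuracy of the three methods is part of the first objective, and the results are meant to guide the choice of method for surveillance. Two things are at stake:

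- Nobody can read from the article what difference in energy error the study is able to detect.
- If the mixed model is non-significant, a reader who takes the power sentence at face value may conclude that the study had 90% power and the methods are equally accurate. A non-significant difference test does not support that.

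**Working it through.** **Inputs from the Protocol article**

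- 150 randomized, 20% dropout, 90% power, 5% level, true difference 0 (Sample and Recruitment). Sidedness is not stated.
- Within-person crossover of three methods (Study Design).
- Test for differences between methods (Energy Intake Estimation Accuracy), at P<.05 (Correlates of Energy Misestimation).

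Completers: 150 × (1 − 0.20) = 120, and 120 / 0.80 = 150, so the dropout arithmetic is consistent. Below, SD means the SD across participants of the difference between two methods' errors (reported minus observed energy). The mixed model is approximated by the paired comparison of two methods.

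**1. Trying to reproduce the stated 90% with the planned test**

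Two-sided rejection probability at zero = 2 × [1 − Φ(1.960)] = 0.050. It is the same for 120, 125, 150, 180 or 188 participants, which covers the usual ways of applying the dropout allowance. A one-sided 5% test also gives 0.050.

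Simulation with 120 completers, three methods and no true difference (20,000 runs):

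| Test | Rejection rate at zero |
|---|---|
| One pairwise comparison | 4.9% |
| Overall three-method test | 5.5% |
| At least one of three unadjusted pairs | 12.5% |

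None is near 90%, so the stated figure does not reproduce.

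**2. What the difference test can detect**

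Detectable difference at 90% power = (1.960 + 1.2816) / √n × SD.

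- n = 120: 3.2416 / 10.954 = 0.296 SD
- n = 150: 3.2416 / 12.247 = 0.265 SD

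Power from the noncentral t distribution with 120 completers is 19% at 0.1 SD, 58% at 0.2 SD and 90% at 0.3 SD.

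The article gives no SD. For an assumed range:

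- 0.296 × 2000 kJ = 592 kJ
- 0.296 × 4000 kJ = 1184 kJ

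**3. What the sentence would mean if equivalence was intended**

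For two one-sided tests (TOST) at 5% each with a true difference of zero, power = 2Φ(margin × √n / SD − 1.645) − 1. Setting this to 0.90 gives margin = (1.645 + 1.645) / √n × SD.

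- n = 120: 3.290 / 10.954 = 0.300 SD
- n = 150: 3.290 / 12.247 = 0.269 SD

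At 2.5% each side, the margins are 0.329 SD (n = 120) and 0.294 SD (n = 150).

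In simulation with 120 completers, equal error variances and a margin of 0.30 SD at 5% each side, one pair is shown equivalent 90% of the time and all three pairs together about 76% of the time.

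**The case against.** The strongest reply is that the sentence is phrased as an equivalence calculation is phrased, and that the number can be made coherent: 120 completers give 90% power at zero for a margin of about 0.30 SD, and 120 / 0.80 = 150. On that view nothing was miscalculated, and the margin and SD are inputs that a journal article may leave to the full protocol or analysis plan. Bland-Altman agreement is also planned, so the energy analysis is not only a search for differences. No section says that a non-significant result will be read as equal accuracy, and the cost-effectiveness sections rely on absolute percentage error, not on the mixed-model P value.

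Several of these points stand. The number 150 is not shown to be inadequate. The absence of a margin or SD would not by itself be a fault in an article. The kJ range is an assumption. The figures for any or all of three pairs go beyond the sentence, which speaks of any two methods. The misreading of a null result is a risk, not a stated intention.

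The central point is not answered. The article gives a power figure with its condition, and also gives the test; the two are incompatible. The Bland-Altman plots compare each recall method with observed intake, not one method with another, so they are not the missing equivalence test. An unseen analysis plan could supply a margin, but it could not make these two statements agree as they stand.

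**Conclusion.** The concern holds. For the planned test, the probability of rejection at a true difference of zero is 5% per comparison, against a stated 90%. Either the figure is wrong for the analysis described, or it belongs to an equivalence analysis that the article does not describe. This needs correcting because it is the sole sample-size justification for the first objective.

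The fault lies in the stated basis, not demonstrably in the sample size. Given 120 completers, a two-sided 5% level and a paired comparison of two methods, the study has 90% power for about 0.30 SD of the within-person difference. The 5% result needs no assumption about the SD; any value in kJ does.

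**What to change.** Choose the question and make the sample-size sentence and the analysis agree.

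**If the question is difference**, replace the sentence with wording such as:

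> With 120 completers (150 randomized, 20% dropout), each pairwise within-person comparison has 90% power at a two-sided 5% level to detect a true difference of 0.30 SD of the within-person difference in (reported − observed) energy intake.

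Add the assumed SD, its source and the resulting value in kJ. Say whether a difference of that size matters, since 0.30 SD is solved back from 120 completers and is not itself a justification.

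**If the question is equivalence**, state the margin and the SD, and analyse each pair by TOST (90% confidence interval wholly inside the margin). Say whether the claim concerns single pairs or all three, because power for all three jointly is lower.

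In either case, state that a non-significant mixed-model result will not be reported as equal accuracy.

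**Cost:** for the difference wording, text only, with no change to enrolment or data collection. For equivalence, one added analysis; if the intended margin is tighter than about 0.30 SD, 150 would need review. The article places data analysis in 2022, after recruitment ends, so the wording should be settled before analysis starts.
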